# Assessment of the effect of addition of 24 hours of oral tranexamic acid post-operatively to a single intraoperative intravenous dose of tranexamic acid on calculated blood loss following primary hip and knee arthroplasty (TRAC-24): a study protocol for a randomised controlled trial

**DOI:** 10.1186/s13063-018-2784-3

**Published:** 2018-07-31

**Keywords:** Tranexamic acid, Blood loss, Hip, Knee, Arthroplasty, Replacement, Post-operative, Oral

## Abstract

**Background:**

While it is has been proven that tranexamic acid (TXA) reduces blood loss in primary total hip and knee arthroplasty (THA and TKA), there is little published evidence on the use of TXA beyond 3 h post-operatively. Most blood loss occurs after wound closure and the primary aim of this study is to determine if the use of oral TXA post-operatively for up to 24 h will reduce calculated blood loss at 48 h beyond an intra-operative intravenous bolus alone following primary THA and TKA. To date, most TXA studies have excluded patients with a history of thromboembolic disease.

**Methods/design:**

This is a phase IV, single-centred, open-label, parallel-group, randomised controlled trial. Participants are randomised to one of three groups: group 1, an intravenous (IV) bolus of TXA peri-operatively plus oral TXA post-operatively for 24 h; group 2, an IV bolus of TXA peri-operatively or group 3, standard care (no TXA). Eligible participants, including those with a history of thromboembolic disease, are allocated to these groups with a 2:2:1 allocation ratio. The primary outcome is the indirectly calculated blood loss 48 h after surgery. Researchers and patients are not blinded to the treatment; however, staff processing blood samples are. Originally 1166 participants were required to complete this study, 583 THA and 583 TKA. However, following an interim analysis after 100 THA and 100 TKA participants had been recruited to the study, the data monitoring ethics committee recommended stopping group 3 (standard care).

**Discussion:**

TRAC-24 will help to determine whether an extended TXA dosing regimen can further reduce blood loss following primary THA and TKA. By including patients with a history of thromboembolic disease, this study will add to our understanding of the safety profile of TXA in this clinical situation.

**Trial registration:**

ISRCTN registry, ISRCTN58790500. Registered on 3 June 2016, EudraCT: 2015–002661-36.

**Electronic supplementary material:**

The online version of this article (10.1186/s13063-018-2784-3) contains supplementary material, which is available to authorized users.

## Background

Increased peri-operative and post-operative blood loss following total hip arthroplasty (THA) and total knee arthroplasty (TKA) can significantly influence the morbidity and mortality for both procedures [1]. Expected blood loss in these operations can range between 500 and 1600 mL [2, 3]. The resulting anaemia increases a patient’s risk of cardiovascular and respiratory complications, increases infection rates and impedes functional mobility.

Tranexamic acid (TXA) is well established in many areas of medicine for reducing blood loss [4] and is a mainstay in the management of traumatic haemorrhage in the emergency department [5, 6]. In lower limb arthroplasty, two meta-analyses of randomised controlled trials using TXA in THA and TKA concluded in favour of its use to limit blood loss [7, 8]. TXA in elective arthroplasty is not yet supported by the National Institute for Health and Care Excellence or British Orthopaedic Association guidelines. In part, this is because, despite a lack of published evidence, there are theoretical concerns about the potential increased risk of venous thromboembolism (VTE) with TXA [9]. Other countries, such as the USA, have embraced the use of TXA in arthroplasty [10–12], favouring the proven benefit of reduced blood loss in these typically elderly patients over the theoretical risk of VTE. To date, there have been no published safety concerns with this approach. A further issue with widespread TXA adoption is the absence of an established standard treatment regime in elective joint arthroplasty. As such, published studies describe a range of doses, routes of administration and durations of treatment [13–17].

Since the study protocol was first authorised for this trial in 2015, a wealth of studies has been published on TXA use in THA and TKA further advocating its use. However, determination of the most effective duration of TXA treatment, dosage and regimen for major joint arthroplasty has barely been investigated. Most studies focus on the intra-operative period [18, 19] with little published work into treatment regimes that extend beyond a dose 3 h post-operatively. However, we postulate that the period of greatest importance is the first 24 post-operative hours. This theory is based upon an internal audit carried out at Musgrave Park Hospital, Belfast, Northern Ireland, on 361 consecutive patients undergoing THA. We compared patients’ intra-operative blood loss to their total blood loss at 2 days post-operatively. Total blood loss was calculated indirectly using equations based on a change in haematocrit [20, 21]. The average directly measured intra-operative blood loss was 223 mL (range 50–1204 mL) and the average indirectly calculated total blood loss was 1377 mL (range 263–3864 mL). On average, the total loss was over six times the measured loss in theatre. Other relevant findings from this audit were that on average 90% of total loss occurs in the first 24 post-operative hours and that intra-operative blood loss grossly underestimates total blood loss, thus making it a poor predictor of total loss. Based on this audit and other literature demonstrating that blood loss continues in the first 24 h post-operatively [22–26], we hypothesise that using TXA up to 24 h post-operatively has the potential to reduce blood loss further following THA and TKA, compared to a single peri-operative dose of TXA. Since there is evidence that oral administration is equally efficacious as intravenous administration [27, 28], this study uses oral TXA post-operatively as a cheaper and less labour-intensive mode of delivery than either IV bolus or infusion regimes.

TRAC-24 will help to define the optimum treatment protocol for TXA use for peri-operative blood loss management in lower limb arthroplasty and will inform the standard of care both at the study site and elsewhere in relation to the use of peri-operative TXA. TRAC-24 will also contribute to the evidence base regarding TXA use and the risk of peri-operative venous and arterial thromboembolism. However, to determine definitively what impact TXA has on VTE in the peri-operative period, a larger-scale multi-centre study would be required.

### Objectives

The primary objective is to determine if the use of oral TXA post-operatively for up to 24 h will confer a reduction in calculated blood loss at 48 h beyond an intra-operative intravenous bolus alone for patients undergoing unilateral primary THA or TKA.

The secondary objective is to determine if the addition of oral TXA post-operatively to an intra-operative intravenous bolus of TXA produces any change in other measurable parameters compared to those observed for either an intra-operative intravenous bolus alone or no TXA for patients undergoing unilateral primary THA or TKA.

## Methods/design

### Study design

This is a phase IV, single-centred, open-label, parallel-group, randomised controlled trial assessing superiority. Elective primary THA and TKA patients are allocated to either one of two TXA intervention groups or one non-treatment comparator group. A study flowchart is shown in Fig. 1. The protocol was written in accordance with the Standard Protocol Items: Recommendations for Interventional Trials (SPIRIT). A SPIRIT figure can be seen in Fig. 2. The SPIRIT checklist is given in Additional file 1.

**Fig. 1 Fig1:**
[figure not shown]
Flowchart for study participants. IV intravenous, OHS Oxford hip score, OKS Oxford knee score, Op operative, TXA tranexamic acid

**Fig. 2 Fig2:**
[figure not shown]
Schedule of enrolment, intervention and assessments. CRP C-reactive protein, Hb haemoglobin, Hct haematocrit, IV intravenous, INR International normalised ratio, KTS knife to skin, OHS Oxford hip score, OKS Oxford knee score, TXA tranexamic acid

When the study was initially planned, the peri-operative use of TXA was not a standard of care in primary THA and TKA in the UK and local site policy reserved its use for patients considered at high bleeding risk. Therefore, the no-intervention control group was deemed necessary to reflect current practice. However, following an interim analysis and review of safety data, which was performed as part of a scheduled data monitoring and ethics committee (DMEC) meeting, it was recommended that randomisation to control group 3 be discontinued. This DMEC meeting took place after 200 participants (40 of whom were in control group 3) had been recruited. By the time approval was gained for this protocol change, 134 participants had been recruited to the control group.

### Primary outcome measure

The primary outcome measure is the total calculated volume of blood loss, in millilitres, at 48 h. This is calculated indirectly, from a series of equations [20, 21, 29].

The first equation determines the patient’s blood volume in litres:$$ \mathrm{PBV}=\left({k}_1\times {h}^3\right)+\left({k}_2\times w\right)+{k}_3, $$

where

PBV = patient’s blood volume (L),

*h* = height (m),

*w* = weight (kg),

*k*_1_ = 0.3669 for men and 0.3561 for women,

*k*_2_ = 0.03219 for men and 0.03308 for women

and

*k*_3_ = 0.6041 for men and 0.1833 for women.

The second equation determines the volume of red blood cells lost in the period from immediately before the operation to 48-h post operatively. Note that PBV should be converted to millilitres prior to calculation of RBC.$$ \mathrm{RBC}=\mathrm{PBV}\times \left({\mathrm{Hct}}_{\mathrm{pre}\hbox{-} \mathrm{op}}-{\mathrm{Hct}}_{\mathrm{post}\hbox{-} \mathrm{op}48\mathrm{h}}\right), $$

where

RBC = red blood cell volume loss (mL),

Hct_pre-op_ = pre-operative haematocrit

and

Hct_post-op 48h_ = post-operative haematocrit.

The third and final equation converts red cell volume loss into whole blood volume loss. We selected the Gross formula for this [29] and adapted it to incorporate transfusions as per the Mercuriali formula [21].

To convert red blood cell volume loss into total blood volume loss, the RBC must be divided by the average Hct. In addition, volume of transfused blood must be taken into account. An average unit of blood has a volume of 280ml with an Hct of 0.6, which is the red cell equivalent of 168mls with an Hct of 1.0. As this is diluted by patient blood volume, the value must again be divided by average Hct.

The Gross formula (adapted assuming an average Packed Red Cells (PRC) unit is 280 mL with a Hct of 0.6) is$$ \mathrm{Total}\kern0.5em \mathrm{volume}\kern0.5em \mathrm{loss}=\frac{\mathrm{RBC}}{{\mathrm{Hct}}_{\mathrm{avg}}}+\left(\left(\mathrm{No}\kern0.5em \mathrm{units}\kern0.5em \mathrm{PRCs}\times 168\right)/{\mathrm{Hct}}_{\mathrm{avg}}\right), $$

where$$ {\mathrm{Hct}}_{\mathrm{avg}}=\frac{\left({\mathrm{Hct}}_{\mathrm{pre}\hbox{-} \mathrm{op}}+{\mathrm{Hct}}_{\mathrm{post}\hbox{-} \mathrm{op}48\mathrm{h}}\right)}{2}. $$

The resultant total volume loss is the primary outcome measure. Traditionally, the primary outcome measure in TXA studies has been transfusion rate. The incidence of transfusion at the study site for TKA patients reduced from 76.0% in 2001 to 5.8% in 2013. This fall preceded TXA use and was a consequence of a more restrictive transfusion policy. Consequently, because transfusion rates are now relatively low, transfusion was not considered to be the most relevant primary outcome measure. As the primary outcome measure, total volume loss is independent of clinician or investigator bias, effectively becoming a blinded outcome measure. Transfusion is more vulnerable to bias because although a transfusion trigger is set prior to surgery, it is simply a prompt for clinicians to consider transfusion and not necessarily to transfuse. Essentially fit patients <65 years have a trigger of <70 g/L and those >65 a trigger of <80 g/L. All those with potential risk factors have a trigger of <90 g/L and symptomatic patients a trigger of <10 g/L.

The study also has a number of secondary and exploratory outcomes. The secondary outcomes characterise other benefits of the interventions for patients undergoing primary THA or TKA. Exploratory outcome measures will not be evaluated to the same extent as the primary and secondary outcomes but have the potential to generate future studies.

### Secondary outcome measures

The secondary outcomes are:Incidence of post-operative haemoglobin (Hb) falling below the transfusion trigger (irrespective of transfusion) prior to dischargeEffect of body mass index on the volume of indirect blood loss at 48 h post-surgeryChange in C-reactive protein (CRP) level from pre-operative to 48 h post-operativeChange in creatinine level from pre-operative to 48 h post-operative90-day mortalityyear mortality

### Exploratory outcome measures

Exploratory outcomes include:Comparison of intra-operative blood loss between the groupsNumber of wound dressing changes in the first 48 h post-operativelyRequests (and results) for post-operative troponin levels prior to dischargePost-operative length of hospital stayIncidence of allogenic blood transfusion prior to dischargeIncidence of allogenic blood transfusion within 90 days of surgeryIncidence of post-operative Hb falling below the transfusion trigger without the patient being transfused to time of dischargeIncidence of post-operative arrhythmia within 90 days of surgeryIncidence of s within 90 days of surgeryIncidence of proximal deep vein thrombosis within 90 days of surgeryIncidence of myocardial infarction within 90 days of surgeryIncidence of cerebrovascular accidents within 90 days of surgeryEmergency hospital admission or unplanned critical care admission within 90 days of surgeryNumber of returns to theatre for wound problems within 90 days of surgeryDifference in indirect blood loss at 48 h between patients on aspirin as a VTE prophylaxis compared with those on enoxaparinDifference in indirect blood loss at 48 h between patients placed in flexion in a knee jig for 6 h post-operatively as opposed to those placed in flexion on a pillowDifference in indirect blood loss at 48 h between patients for whom a tourniquet was used compared to those for whom a tourniquet was not used during TKAChange in Oxford hip score (OHS) or Oxford knee score (OKS) from pre-operatively to 90 days post-operativelyChange in OHS or OKS from pre-surgery to 1-year post-surgeryDifferences in hospital costs associated with each treatment group

The OHS and OKS are outcome measures [30] widely used pre- and post-operatively for all patients at the study site to measure the success of an operation. It will be important to ensure that there are no differences in OHS/OKS at 1 year between each of the groups. The OKS/OHS is assessed for patients by hospital staff at their pre-operative assessment clinic, at the 90 day follow-up review clinic (for TKA patients only) and at the patient’s 1-year clinic as part of standard care. Patients must attend their pre-operative assessment clinic, but should any patient be unable to attend a post-operative clinic, the OHS/OKS will be completed via telephone. THA patients have an early post-operative clinic at 6 weeks routinely, so for this study the 90-day OHS is assessed over the telephone by research nurses. Because the participants are not blinded to their intervention, there is the potential for bias when completing the Oxford scores at 90 days and 1 year following surgery. Practically, we feel any such effect would be negligible.

The incidence of death and complications at 90-days post-operatively are clinically important outcomes for this study. While this study is not powered to answer whether the use of TXA can lower complications, it is important that complications are reported.

### Study setting

This is a single-centre study taking place in a Primary Joint Unit in a regional orthopaedic centre in the UK with patients under the care of one of four consultant orthopaedic surgeons being recruited to the study.

### Study participants

Participants who are on the waiting list for a primary THA or TKA within the Primary Joint Unit are screened for study inclusion.

### Inclusion criteria

The following inclusion applies:Awaiting primary elective THA or TKA≥18 years and ≤100 years of age

### Exclusion criteria

The exclusion criteria for this trial are:Do not pass a pre-operative assessment for elective THA or TKAFractured neck of femurHaemophiliac or coagulation disorders that require TXAAllergy to TXA or any of its excipientsPlatelets less than 75,000/mm^3^ at pre-operative assessment*Active treatment for deep VTE or pulmonary embolism within 6 months prior to surgery*History of VTE within 6 months prior to surgery*Myocardial infarction within 12 months prior to surgery*Cardiac stent within 12 months prior to surgery*Cerebrovascular accident or transient ischemic attack within 9 months prior to surgery*Use of antiplatelet medication within 7 days prior to surgery* (does not include aspirin if dose <300 mg).Direct thrombin inhibitors within 2 days prior to surgery*Factor Xa inhibitors within 2 days prior to surgery*The international normalised ratio is greater than or equal to 1.5 in a patient who has stopped warfarin in preparation for surgeryHepatic failure*History of epilepsyRequiring therapeutic anticoagulation post-operatively, e.g. due to a metallic heart valvePregnant women, women who have not yet reached the menopause (no menses for ≥12 months without an alternative medical cause) who test positive for pregnancy or are unwilling to take a pregnancy test prior to trial entryHave been using combined hormonal contraception (which includes combined oral contraception, a combined contraceptive transdermal patch and a vaginal ring) within 4 weeks prior to surgery*Female patients who are breastfeedingTreated with any other investigational medication or device within 60 days prior to surgeryUnable to provide informed consentUnable or unwilling to commit to the study schedule of eventsUnwilling to provide informed consentPresent for simultaneous bilateral THA or TKAOn renal dialysis and have an arteriovenous fistulaHave previously been enrolled in this study

*These patients at the study site have contra-indications to primary THA/TKA.

### Recruitment and consent

TRAC-24 originally required a minimum of 1166 patients to be recruited. Recruitment would stop when 583 participants were recruited for both TKA and THA. However, following a DMEC recommendation, recruitment to control group 3 was stopped, after approval from the sponsor, the regional ethics committee and the Medicines and Healthcare Products Regulatory Agency (MHRA) was acquired. At this point, 672 participants had been recruited to the study. This meant that a minimum of 466 THA and 466 TKA were now required to complete the study with a minimum overall recruitment of 1066, recruiting only to groups 1 and 2. Potentially eligible patients are identified and screened by members of the clinical study team based on the inclusion and exclusion criteria outlined above.

A cover letter and a patient information sheet approved by the Research Ethics Committee is sent to potential patients informing them about the study. The latter contains a contact number should they have any questions or wish to discuss the study further. The study is then discussed directly with the patient at a pre-operative clinic (approximately 7 to 10 days prior to operation) or following admission for surgery. Informed consent is taken by a member of the research team after the participant has been given the opportunity to ask further questions and agrees to participate.

### Study assessments

All patients are evaluated during the study according to the schedule of enrolment, interventions and assessments as outlined in Fig. 2. Data are collected at each of the following time points: pre-operatively, intra-operatively, post-operatively until discharge and then at 90 days and 1 year post-operatively.

### Randomisation and blinding procedures

At the outset of the trial, eligible participants were allocated to intervention group 1, intervention group 2 or control group 3 (standard care) with an allocation ratio of 2:2:1. After the DMEC recommended stopping randomisation to control group 3, eligible participants were then allocated to intervention group 1 or intervention group 2 with an allocation ratio of 1:1. Blocked randomisation with randomly permuted block sizes is used. Participants are stratified according to operation type, surgeon and creatinine level, resulting in 16 possible stratifications (Fig. 3):

**Fig. 3 Fig3:**
[figure not shown]
Stratification factors. THA total hip arthroplasty, TKA total knee arthroplasty

The randomisation sequence is concealed using sealed envelopes with tamper-proof labels. The trial statistician generated the randomisation sequence. When a participant has been recruited, consented and admitted to the ward pre-operatively, a sealed envelope is opened in sequence according to the stratification. Two members of the research team must be present for this. The envelope is not opened until the post-operative transfusion trigger has been recorded, which is set after consent and prior to randomisation. Anaesthetists, surgeons, and other theatre, recovery and ward staff will not be blinded to the treatment, nor will the study investigators or the patient themselves. The decision to transfuse is not blinded but the transfusion trigger is blinded. This means that the number of patients falling below that transfusion trigger is blinded. Laboratory staff who process the blood samples are blinded to the treatment allocation.

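### The count of patients below the transfusion trigger is called blinded, but the open-label design protects only the threshold and the laboratory assay

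*Protocol article*

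**What the plan says.** The Study design section describes the trial plainly: "This is a phase IV, single-centred, open-label, parallel-group, randomised controlled trial assessing superiority". Randomisation and blinding procedures then says who knows the allocation: "Anaesthetists, surgeons, and other theatre, recovery and ward staff will not be blinded to the treatment". The same sentence adds the investigators and the patients.

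Two steps are protected. On the threshold: "The envelope is not opened until the post-operative transfusion trigger has been recorded, which is set after consent and prior to randomisation". On the assay: "Laboratory staff who process the blood samples are blinded to the treatment allocation".

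Between these, the section separates the decision from the threshold: "The decision to transfuse is not blinded but the transfusion trigger is blinded". It then concludes: "This means that the number of patients falling below that transfusion trigger is blinded".

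The outcome concerned is the first under Secondary outcome measures. It asks whether a post-operative Hb drops under the patient's trigger at any time up to discharge, whether or not blood is given. Study assessments refers to Fig. 2 for the schedule. The figure is not shown, but its caption lists both Hb and haematocrit.

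**The concern.** An outcome of the form *any value below a cut-off during the stay* depends on the cut-off, the measured values, and the times at which values exist. The article argues from the first to the whole. Fixing the cut-off before allocation does not blind how long the patient is observed, whether extra samples are taken, or whether a transfusion changes the values that follow.

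A reader told that the count is blinded will give it more trust than an open-label trial can support. If one arm is observed for longer or sampled more often, it has more chances to record a low value, and the arms could differ with no difference in true Hb course.

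**Working it through.** No stated figure is in dispute, so the main check sets the article's statements side by side.

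| Element of the outcome | What the article says | Blinded? |
|---|---|---|
| Threshold | Recorded before the envelope is opened | Yes, by timing |
| Assay | Laboratory staff do not know the allocation | Yes |
| Observation window | Ends at discharge, no fixed hour; ward staff know the allocation | No |
| Hb tests within the schedule | In Fig. 2, not shown | Cannot be judged; if scheduled, frequency is fixed by protocol |
| Hb tests beyond the schedule | No statement | Not shown to be |
| Transfusion | Decision stated to be unblinded | No |

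On the last row, a patient already recorded below the trigger stays counted whatever happens next. Transfusion matters only for a patient who receives blood before any sub-trigger value is recorded. The article neither describes nor excludes this; Study drug says no relevant concomitant care is permitted or prohibited.

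**Contrast with the primary outcome.** Its haematocrit is taken at a fixed 48 h, and its formula adds back transfused units. The length of the window and the number of tests do not enter it.

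**Illustration of size (all rates assumed).** Suppose there is no true effect, a proportion p is detected below the trigger in one arm, and the other arm has r times as many independent detection opportunities. Then

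p₂ = 1 − (1 − p)^r, d = p₂ − p.

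For the two-sided 5% pooled two-proportion test (equivalent to the planned chi-squared test without continuity correction), with n per arm:

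rejection probability = Φ((d − 1.96·se₀)/se₁) + Φ((−d − 1.96·se₀)/se₁),

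where se₀ = √(2·p̄(1 − p̄)/n), p̄ = (p + p₂)/2, and se₁ = √((p(1 − p) + p₂(1 − p₂))/n).

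The arm sizes come from Statistical and interim analysis: 233 per arm for each joint, 466 for both joints combined.

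Worked case, p = 0.10, r = 1.25, n = 233:
- p₂ = 1 − 0.90^1.25 = 0.1234, so d = 0.0234 and p̄ = 0.1117.
- se₀ ≈ se₁ ≈ 0.0292.
- Φ((0.0234 − 0.0572)/0.0292) + Φ((−0.0234 − 0.0572)/0.0292) = Φ(−1.16) + Φ(−2.76) ≈ 0.123 + 0.003 = 12.6%.

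Rejection rates of the nominal 5% test, 233 / 466 per arm:

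| Assumed p | r = 1.1 | r = 1.25 | r = 1.5 |
|---|---|---|---|
| 6% | 5.8% / 6.5% | 9.5% / 14.2% | 21.8% / 38.5% |
| 10% | 6.3% / 7.6% | 12.6% / 20.5% | 32.9% / 57.4% |
| 20% | 7.5% / 10.2% | 20.3% / 35.8% | 56.7% / 85.4% |

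A 10% imbalance adds roughly 1 to 5 percentage points to the error rate; 25 to 50% would be material. Nothing in the article shows that any such imbalance exists.

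**The case against.** The strongest defence is that the sentence, read in context, only contrasts this outcome with the decision to transfuse. The preceding sentences tell the reader who is unblinded. Hb is an objective laboratory value, the laboratory is blinded, the cut-off is fixed in advance, and counting patients whether or not they receive blood removes the discretion to withhold it. Fig. 2 may schedule every Hb test that matters. The internal audit of hip patients in the Background found that on average 90% of total loss occurs in the first 24 post-operative hours, which limits new bleeding late in the stay.

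Much of this stands. It makes the outcome better protected than transfusion itself and leaves the bias possible rather than shown. It does not make the count blinded: the window still ends at discharge, and a schedule would protect only the part of the stay that it covers.

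A reader might infer several stronger points that the article does not support:
- **That it allows transfusion above the trigger.** Primary outcome measure says of the trigger that "it is simply a prompt for clinicians to consider transfusion and not necessarily to transfuse". That is discretion not to transfuse once the trigger is reached; it is silent on transfusion above it.
- **That length of stay is expected to differ by arm.** It is only listed among the exploratory outcomes.
- **That this outcome was chosen because transfusion is open to bias.** That argument is made for choosing calculated blood loss as the primary outcome.
- **That ward staff decide how many Hb samples are taken.** Without Fig. 2 this cannot be known.

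**Conclusion.** The claim that the count is blinded does not follow from the design and should be corrected. The article secures a threshold set before allocation and a blinded assay. It does not secure a blinded observation window, blinded testing beyond the schedule, or freedom from the effect of an unblinded transfusion decision on later Hb values.

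The possible bias is of unknown size and direction. The rejection rates above are conditional on assumed base rates and imbalances and are not estimates for this trial. The conclusion takes the trigger as fixed once recorded, as Randomisation and blinding procedures states.

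The point affects one secondary outcome. It would be wrong to infer that the primary outcome is compromised by this route, since it rests on a fixed 48 h sample.

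**What to change.** 1. In Randomisation and blinding procedures, replace the claim about the count. Say that each patient's trigger is set before allocation is known and that the assay is done by blinded laboratory staff. Do not describe the number of patients below the trigger as blinded.
2. Keep the to-discharge outcome as defined. With 879 participants recruited by the end of February 2018 against a minimum of 1066, replacing it now would be a debatable trade.
3. Add an analysis restricted to protocol-scheduled post-operative Hb values up to and including the 48 h sample. This assumes that Hb is reported from the 48 h blood sample that already supplies the primary-outcome haematocrit.
4. Report length of stay by arm beside both analyses and, where recorded, the number of Hb tests per patient.

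Patients should not be counted as events merely because they were transfused: that would bring the unblinded decision back into the outcome.

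The cost is one sentence, under the usual approval for protocol changes, and a little extra analysis that can go into the analysis plan still to be approved before analyses begin. Falls first recorded after 48 h are not counted in the added analysis but remain in the main one. The article does not show whether test counts are recorded, so that item depends on the case report form.
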